## Methods

### Study Aim

Recognizing the critical role of recovery during intermittent or RSA performance, the anti-fatigue effects of H_2_ and its impact on mitochondrial ATP synthesis support the hypothesis that acute pre-exercise HRW administration, compared with a placebo, may positively affect biochemical, perceptual, and neuromuscular performance variables during a 72-hour period after a simulated football match. This study aims to assess the impact of pre-exercise HRW administration compared with a placebo on biochemical, perceptual, and performance variables within 72 hours after a simulated football match. The specific aims are to assess the impact of pre-exercise HRW administration on acute neuromuscular performance decrement, the impact of pre-exercise HRW administration on acute muscle soreness and the CK levels of players, and the impact of pre-exercise HRW administration on residual muscle fatigue and duration of return to readiness to play.

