#### Randomization

A stratified block randomization approach will be used to allocate participants into intervention groups. Participants will be stratified based on their playing position into three distinct strata: (1) defenders, (2) midfielders, and (3) forwards. Within each stratum, participants will be randomly assigned in a 1:1 ratio to either the HRW group or the placebo group using a fixed block randomization method. Randomization sequences will be generated using a robust randomization algorithm, as described by Tu and Benn [28], and implemented via a secure web-based allocation system.

Following participant selection and baseline assessment, each participant will receive either HRW or a placebo in visually identical plastic-aluminum packs, with group allocation determined by the pregenerated randomization code. This process ensures allocation concealment and maintains blinding throughout the study.

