#### Sample Size and Power Analysis

The sensitivity analysis was performed using G*Power (Version 3.1, Heinrich-Heine-Universität). Considering a type 1 error of 0.05 (α=.05) and a test power of 80% (β=.15), the calculated sample size for repeated measures (within and between interaction) is 22 participants with 11 in each group. Considering a 10% sample loss, a total of 24 participants will be recruited for the study.

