#### Statistical Analyses

Statistical analysis and data management will be undertaken using SPSS version 22.0 software (IBM Corp), using an α≤.05. The normality and homogeneity of all data will be verified with the Shapiro-Wilk and Levene tests. Mean and SD will be calculated for each outcome measure with a parametric distribution and medians and quartiles for data with a nonparametric distribution. A repeated-measures ANOVA with one random factor as subject, two fixed factors as type of water (HRW/placebo) and time (prematch; postmatch; and 24, 36, and 72 hours post match), and mutual interaction of water and time will be used to assess acute and residual fatigue. When a significant effect of time or water is observed, pairwise comparisons will be performed using Tukey post hoc test. η^2^_p_ was used as a measure of effect size for each analysis of variance, and values were interpreted as having a small effect (0.01≤η^2^_p_<0.06), medium effect (0.06≤η^2^_p_<0.14), and large effect (η^2^_p_≥0.14).

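### Separate acute and residual aims rest on one 4-df water-by-time interaction, with no between-arm contrast or follow-up that says which aim is met

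*Protocol article*

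**What the plan says.** Study Aim separates the questions. Among the specific aims are "the impact of pre-exercise HRW administration on acute neuromuscular performance decrement" and "the impact of pre-exercise HRW administration on residual muscle fatigue and duration of return to readiness to play"; a third concerns acute soreness and creatine kinase. The three therefore group into acute and residual. Study Design follows the same split: the postmatch assessment is for acute fatigue and the three later ones are for residual fatigue.

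Statistical Analyses describes one repeated-measures ANOVA with subject as random factor, water and time as fixed factors, and their interaction. The sentence ends: "mutual interaction of water and time will be used to assess acute and residual fatigue". Tukey pairwise comparisons follow when time or water is significant. The interaction is not named as a trigger, and no contrast is tied to an aim.

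Sample Size and Power Analysis sizes the trial on the same term: "the calculated sample size for repeated measures (within and between interaction) is 22 participants with 11 in each group".

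**The concern.** The arms start level by randomisation, so the effect of hydrogen-rich water appears as a difference in change from prematch. Only water-by-time tests that, and it tests all patterns of change together. It can be significant because of a postmatch difference alone, a difference on one recovery day, or a difference throughout.

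The other terms do not fill the gap. Time effects are pooled over arms and say nothing about active against placebo. The water main effect averages over all five time points, prematch included, and has two levels, so a Tukey step on it adds nothing.

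Followed as written, the plan yields no between-arm test or estimate for either aim. The Conclusions of the Abstract look ahead to readiness to train and microcycle planning, which need an estimate specific to the recovery days.

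**Working it through.** **1. Degrees of freedom.** Two arms and five time points give (2−1)(5−1) = 4. The fourth time point is 36 h in Statistical Analyses and 48 h in Study Design; the count is five either way.

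**2. The plan's own figure.** For the within-between interaction, λ = f²·N·m/(1−ρ), with df 4 and (N−2)·4. The article states neither f nor ρ. Assuming f = 0.25, ρ = 0.5, sphericity and m = 5:
- N = 22: λ = 0.0625 × 22 × 5 / 0.5 = 13.75, df 4 and 80, power 83.6%.
- N = 20: λ = 12.5, df 4 and 72, power 79.1%.

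So 22 is the smallest even total reaching 80% under these assumptions. This is consistent with the trial being sized on the 4-df interaction.

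**3. The interaction cannot tell the aims apart.** Assume 11 per arm, unit SD, equal correlation r and an effect of 0.8 SD. Then λ = (11/2)·Σ(dⱼ − d̄)²/(1−r), where dⱼ is the arm difference at time j.
- Acute only, d = 0.8 × (0,1,0,0,0): Σ = 0.64 × (1 − 1/5) = 0.512.
- Sustained, d = 0.8 × (0,1,1,1,1): Σ = 0.64 × (4 − 16/5) = 0.512.
- 48 h only: Σ = 0.512.

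At r = 0.5 each gives λ = 5.5 × 0.512 / 0.5 = 5.63. Three different answers to the aims have the same chance of a significant interaction: about 0.42 at r = 0.5 and 0.65 at r = 0.7.

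**4. What aim-specific contrasts would do.** Acute: postmatch minus prematch. Residual: mean of the three later assessments minus prematch. Each is compared between arms on 20 df. The figures come from 20,000 simulated trials per scenario, accurate to about ±0.01. The gated column requires a significant interaction and then the same contrast at .05. Cells show r = 0.5 / r = 0.7.

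| True effect and aim | Contrast at .05 | Gated by interaction | Contrasts with Holm |
|---|---|---|---|
| Sustained, residual aim | 0.59 / 0.80 | 0.38 / 0.63 | 0.50 / 0.73 |
| Sustained, acute aim | 0.43 / 0.63 | 0.30 / 0.53 | 0.38 / 0.60 |
| Acute only, acute aim | 0.43 / 0.63 | 0.30 / 0.53 | 0.32 / 0.51 |
| Residual only, residual aim | 0.59 / 0.80 | 0.48 / 0.75 | 0.47 / 0.71 |

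The first column is not a fair comparison. With no true effect, two unadjusted contrasts give at least one false positive in about 9% of trials, against 5% for the interaction. The Holm column is the fair one.

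**5. Where the averaged residual contrast fails.** For an effect at 48 h only, the contrast sees 0.8/3 = 0.27 SD. Its power at .05 is 0.11 / 0.16, while the interaction rejects in 0.42 / 0.65. For an effect falling from 0.8 SD postmatch through 0.67 and 0.33 of that size to zero at 72 h, it has 0.11 / 0.16 against 0.40 / 0.62.

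**The case against.** **The quoted words end a longer sentence.** Its subject is the whole ANOVA, and the article does not say that the interaction alone decides both aims. That is correct. The point survives because no other term compares the arms' change over time.

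**Localising is the job of the follow-up, and an omnibus test followed by comparisons is standard.** That would answer the point if a follow-up of the interaction were stated. Here the trigger is time or water only.

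**Aim-level contrasts may be in a fuller document that is not shown.** Possibly. But the article itself fixes the model, the trigger and the post hoc test, and what it fixes does not reach the stated aims.

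**A reader might infer that two planned contrasts are generally more powerful.** The documents do not support that. They give no effect size, correlation or expected pattern. In the illustration the advantage is clear only for a sustained effect. It vanishes or reverses for one-phase effects once alpha is shared, and the averaged residual contrast does badly for a one-day or quickly decaying effect. The gated route is also a constructed comparator, since the article plans Tukey tests.

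**A reader might also infer that an acute-only effect will be reported as a residual one.** Nothing in the article says so. The plan leaves that ambiguity open; it does not commit to the misreading.

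**Averaging the recovery days suits the residual aim poorly**, because that aim includes how long the return to readiness takes. This stands, and the fix has to keep the time course.

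**Conclusion.** The point holds as one of interpretability. Separate acute and residual aims are served by a single 4-df interaction that cannot say which is met, and no between-arm contrast or follow-up of it is stated. This follows from the text and from the count of two arms by five times, without any assumption about effect size.

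No general loss of power is established. All power figures above rest on an assumed 0.8 SD effect, equal correlations of 0.5 or 0.7, and 11 per arm. They show how the answer depends on the pattern and are not estimates for this trial. The change is a cheap improvement worth making before the data are unblinded.

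**What to change.** In Statistical Analyses, for each outcome:

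- Name one between-arm contrast per aim. Acute: postmatch minus prematch. Residual: mean of the three later assessments minus prematch. Test each with its own error term (20 df at 11 per arm), which avoids the sphericity assumption. Report each with a 95% CI, and apply Holm across the two.
- Keep the 4-df interaction test.
- Report the between-arm difference in change from prematch, with a CI, at each of the three residual time points, so that the time course needed for return to readiness is not averaged away.

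The cost is a few sentences and no new data. There are two downsides. The averaged residual contrast is insensitive to an effect that is confined to one day or decays quickly; the retained interaction and the time-point estimates partly cover this. Holm also costs some power: in the sustained example at r = 0.5, the residual contrast falls from 0.59 to 0.50.

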### Study Design

This study protocol was designed according to the 2023 SPIRIT (Standard Protocol Items: Recommendations for Interventional Trials) statement [27]. The experimental study will use a robust research design, adopting a randomized, placebo-controlled, double-blinded, parallel structure (see Figure 1 and Multimedia Appendix 1).

To ensure unbiased results, the administration of HRW and the placebo was randomized and counterbalanced. The investigation will be conducted over a carefully planned 2-week period on a grass football field. During the initial session, participants will be familiarized with the Team^2^Pro Polar suite (1.4.5 version) and briefed on the regulations governing a simulated football match. Before the first measured session, participants will be stratified based on their playing positions (defenders, midfielders, and forwards) and subsequently randomized into either the HRW or placebo groups. Neuromuscular performance will be assessed through measures including the 20-meter repeated sprint test and CMJ. Metabolic fatigue will be measured through CK levels and muscle soreness, as reported using a VAS. These assessments will occur at critical time points: during simulated match day (SMD) immediately post warm-up; directly following the simulated football match to detect acute fatigue; and immediately post warm-up at intervals of 24 (SMD + 1 day), 48 (SMD + 2 days), and 72 (SMD + 3 days) hours after training sessions to detect residual fatigue. The first measurement sessions will be systematically scheduled on Monday afternoons, allowing for a standardized 72-hour recovery period following the last training session. To enhance ecological validity, the simulated match was designed according to official football rules officiated by an experienced referee, comprising two 35-minute halves, with 11 players per team and no substitutions allowed. Regarding intensity regulation, all participants will be instructed to perform at match intensity, which will be monitored using heart rate (HR) data and rate of perceived exertion scores. These measures will indicate consistent physiological workload across participants, supporting the comparability of internal load responses. Environmental conditions (eg, temperature, lighting) will be held constant throughout all testing sessions to reduce external variability.

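### The single Tukey follow-up leaves the compared means and the error term open, and on none of its three readings does it give a sound HRW-versus-placebo comparison at each assessment

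*Protocol article*

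**What the plan says.** The Statistical Analyses section specifies "A repeated-measures ANOVA with one random factor as subject, two fixed factors as type of water (HRW/placebo) and time", with five time levels. It adds that the "mutual interaction of water and time will be used to assess acute and residual fatigue", "using an α≤.05". The follow-up is one sentence: "When a significant effect of time or water is observed, pairwise comparisons will be performed using Tukey post hoc test".

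The Study Design section describes the trial as "adopting a randomized, placebo-controlled, double-blinded, parallel structure", and the Randomization section has players "randomly assigned in a 1:1 ratio to either the HRW group or the placebo group". So water is a between-player factor and time a within-player factor.

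The Study Aim section asks about effects of HRW relative to placebo. One aim is "the impact of pre-exercise HRW administration on acute neuromuscular performance decrement"; the others cover acute soreness and CK, and residual fatigue up to 72 hours.

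The follow-up sentence does not say whether Tukey is applied to the levels of the significant factor or to the ten water-by-time cells. It names no error term.

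**The concern.** Tukey's procedure refers differences between means to a studentized range built on one error mean square. It suits means that are independent and share that error. A mixed design has two kinds of comparison. A contrast of times within players carries only within-player variance. A contrast of arms at one time compares different players and carries between-player variance as well. One Tukey procedure with one error cannot serve both.

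The pairwise step is the only follow-up stated that could place an HRW effect at postmatch or at a later assessment. How its open details are filled in therefore decides what the trial can report on its acute and residual aims, for every outcome analysed this way.

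**Working it through.** **Inputs from the protocol.** Two parallel arms at 1:1, five times, α = 0.05, and 22 players (11 per arm) before loss. **Assumptions, not in the protocol:** intraclass correlation (ICC) from 0.3 to 0.9, compound symmetry, total variance 1.

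**The plan's own figure.** For the within-between interaction, λ = f²·N·m/(1−ρ). With assumed f = 0.25 and ρ = 0.5, N = 22 and m = 5, λ = 0.0625 × 22 × 5 / 0.5 = 13.75 on 4 and 80 df. Power is 0.836, and N = 20 gives 0.791. So 22 is reproduced under those assumed inputs, and 11 per arm is used below.

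**Reading 1: marginal means.** Water has two levels, so Tukey equals the t test (critical value 2.086 at 20 df by both). For time, it compares times averaged over the arms. Neither compares HRW with placebo at a given time.

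**Reading 2: ten cells, model residual.**
- True variance of a same-time arm difference: 2/11, so the SE is 0.426.
- Variance the test would use: 2(1−ICC)/11.
- True SE over SE used: 1/√(1−ICC), which is 1.4, 1.8, 2.2 and 3.2 at ICC 0.5, 0.7, 0.8 and 0.9.
- Tukey critical value: q(0.95; 10 means, 80 df) = 4.603, or 4.603/√2 = 3.255 on the t scale.

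In true SE units the bar at ICC 0.8 is 3.255 × √0.2 = 1.46, a two-sided error of about 15% at each time.

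Simulation: 20,000 trials per ICC, no HRW effect, a common time profile of 0, −1, −0.6, −0.3 and −0.1 SD, follow-up run only if the time or water F test was significant (96–100% of trials).

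| ICC | At least one false same-time difference |
|---|---|
| 0.3 | 3.7% |
| 0.5 | 9.6% |
| 0.7 | 21.8% |
| 0.8 | 32.8% |
| 0.9 | 49.9% |

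A second simulation without the F-test gate and with a different time profile gave 3.6%, 9.3%, 21%, 33% and 49%. With 12 per arm the rates are much the same.

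**Reading 3: ten cells, correct between-plus-within error.** Ten cells give 10 × 9/2 = 45 pairs, of which only 5 compare the arms at the same time. The chance of any false same-time difference falls to 0.7–0.9% with 80 df, or 0.3–0.4% with 20 df.

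Power for a 1.0-SD same-time difference (1/0.426 = 2.345 SE, normal approximation):
- Tukey: P(Z > 3.255 − 2.345) = P(Z > 0.91) = 18%.
- Bonferroni over four same-time contrasts, same SE, two-sided α = 0.0125, critical value 2.498: P(Z > 0.153) = 44%. With the t critical value on 80 df (2.555) it is P(Z > 0.21) = 42%.

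**The case against.** The strongest reply is that the harmful reading is not in the text. The section names no error term, and a random subject effect is compatible with testing water against between-player variation. Done that way, the overall HRW-placebo comparison keeps a false-positive rate of 4.8–5.1% at every correlation tried. The sentence can also be read literally as comparing the levels of whichever factor is significant; no 45-pair family then arises. The hypothesis already has its test in the water-by-time interaction, and error strata for follow-up contrasts are detail that an article may leave to a fuller document.

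Most of this stands, and it limits the point. A reader might infer that HRW will be judged against placebo on within-player error, so that ordinary differences between players will be reported as HRW effects. The document does not support that as a statement of fact. Nor would the null hypothesis be wrong on that reading: it remains equality of means, and what would be wrong is the standard error and its degrees of freedom. The inflation also needs comparisons opened by a time effect. If only a correctly tested water effect opened them, the rate would be at most about 5%.

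The reply does not rescue the sentence. Its literal reading is the one that never compares the arms at a given time. A time effect is what the protocol itself expects after a match. The method is named, not left open, and each way of completing it serves the aims poorly.

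**Conclusion.** The point holds as a low-cost improvement, not as proof of an invalid analysis. Depending on the reading, the Tukey step does not address the arm comparison at each time, is anti-conservative, or is needlessly strict. These are alternatives and cannot be added together.

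The 10–50% false-positive rates are conditional on residual error, ten cells, a time-opened follow-up and an assumed ICC of 0.5 or more. At 0.3 the rate is below nominal.

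The like-for-like power loss on the third reading is about 18% against 44%. A larger contrast is tempting: four Bonferroni-adjusted changes from prematch give 87% at ICC 0.8. That sets a change score against a level difference, so most of the gap is not due to Tukey. At ICC 0.5 the change contrast gives 42%, about the same as the same-time level contrast.

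Whether a main effect or the interaction should trigger follow-up tests is a separate question and is not part of this point.

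**What to change.** For arm comparisons, replace the Tukey sentence with pre-specified HRW-minus-placebo contrasts from the same random-subject model, with players nested in arm:

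- Four contrasts per outcome: postmatch and each of the three scheduled later assessments. The time labels need reconciling first: Statistical Analyses lists "prematch; postmatch; and 24, 36, and 72 hours post match", whereas Study Design schedules 24, 48 and 72 hours.
- A standard error matched to each contrast: between-plus-within variance for same-time levels, within-player variance for change from prematch.
- Holm adjustment over the four contrasts, with 95% confidence intervals.
- A statement of whether the same-time level or the change from prematch is the main contrast, with the other reported alongside. This matters because, under Preparation of HRW and Placebo, the first packs are taken 24 hours before the match. The prematch value is therefore not untreated, and subtracting it could remove an early effect.

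Pairwise comparisons of times may stay as secondary results on the within-player error.

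The cost is a short replacement text and some contrast syntax, with no extra players or data. The batch codes stay with the manufacturer until after the analysis (Blinding section), so the change can be made without knowledge of allocation. The downside is that cross-cell comparisons not tied to the aims become descriptive.

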#### CMJ Test and VAS Scale

The CMJ test will be performed on a hardwood indoor surface, commonly used in sports science settings to ensure consistency and reliability of performance measurements. Participants performed 5 jumps and will be instructed to maximize jump height and minimize ground contact time with indoor football shoes. Participants start from an upright standing position with their hands on their hips. The CMJ test will be performed on a mobile optical device, the OptoJump system (Microgate SRL, Italy). Participants will perform three repetitions with a 3-minute recovery; the best attempt will be used. The average height and reactive strength index will be calculated. Reactive strength index will be calculated as jump time divided by contact time [30].

The self-reported perceptual measure by the VAS will be applied to assess lower limb muscle pain [31]. The VAS will be applied just after the CMJ test on a horizontal 100 mm length line with the left and right ends of the line corresponding to “no soreness during repeated maximal jumps” and “most soreness ever experienced during repeated maximal jumps.”

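### The post hoc trigger leaves out the water × time interaction that carries the hypothesis and the sample size; separately, five outcomes unranked in the article, each tested at .05, give about 18–24% family-wise error

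*Protocol article*

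**What the plan says.** All of this stands in the protocol article.

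- **Model (Statistical Analyses).** Subject is a random factor; type of water and time are fixed factors, "and mutual interaction of water and time will be used to assess acute and residual fatigue". The error level is given as "using an α≤.05", with no division across outcomes.
- **Follow-up rule (same section).** "When a significant effect of time or water is observed, pairwise comparisons will be performed using Tukey post hoc test". The interaction is not mentioned. The article does not say which means are compared or with which error term.
- **Sample size (Sample Size and Power Analysis).** "the calculated sample size for repeated measures (within and between interaction) is 22 participants with 11 in each group".
- **Aims (Study Aim).** The specific aims cover acute decrement, acute soreness and CK, and "the impact of pre-exercise HRW administration on residual muscle fatigue and duration of return to readiness to play". One hypothesis spans biochemical, perceptual and neuromuscular variables.
- **Outcomes (Study Design; RSA Measurement; CMJ Test and VAS Scale).** At least five: RSA total time, jump height, reactive strength index, CK and VAS soreness. None is called primary.

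**The concern.** Whether HRW changes the decrement after the match, or the speed of recovery, is a question about different time courses in the two arms. In this model that is the water × time term, and the authors sized the trial on it. A follow-up rule should start from that term and lead to comparisons between arms at the times the aims name. This rule starts from two other terms. One of them, time, is expected to be significant whether or not HRW works, because post-match fatigue is the premise of the study.

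Two things are at stake. If the interaction is significant, the plan gives no agreed way to say when the arms differ, so that choice would be made after seeing the data. If it is not, the time effect still licenses pairwise tests, and a report could rest on one arm being back to its prematch level while the other is not. Testing several unranked outcomes at .05 is a separate source of error.

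**Working it through.** **1. The sample size as a check on which term matters.** The article gives two groups, five times, α = .05 and N = 22. It gives no effect size or correlation, so the figure cannot be reproduced from its own inputs. Assume f = 0.25 and correlation ρ = 0.5. For the within–between interaction, λ = f²·N·m/(1 − ρ) = 0.0625 × 22 × 5 / 0.5 = 13.75, with df (2 − 1)(5 − 1) = 4 and (22 − 2)(5 − 1) = 80. Power is 0.836; the same formula at N = 20 gives 0.791, so 22 is the smallest equal-arm size reaching 80%. For 80% power at N = 22, f must be 0.284, 0.240 or 0.186 at ρ = 0.3, 0.5 or 0.7. The stated 22 is thus consistent with an interaction calculation, as the article says.

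**2. The rule applied literally.**

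| Significant term | Follow-up | Information on HRW |
|---|---|---|
| Time | Tukey on 5 means pooled over arms: 5 × 4 / 2 = 10 pairs | None |
| Water | 2 means, 1 pair | Repeats the F test |
| Water × time | None named | No time-specific comparison |

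**3. The rule read as Tukey over all cells.** Two arms × 5 times = 10 cells and 10 × 9 / 2 = 45 pairs. Of these, 5 compare arms at the same time, 2 × 10 = 20 lie within an arm, and the other 20 mix arm and time. Between-arm pairs now exist, but the time effect opens them. Simulations with no HRW effect (11 per arm, compound symmetry, assumed time means 0/1.2/0.9/0.5/0.2 SD) gave, per outcome:

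- time significant in about 100% of trials, so it screens nothing;
- at least one same-time HRW–placebo pair flagged in about 1% of trials if the error pools between- and within-player variance, but in 9%, 22% and 33% at ρ = 0.5, 0.7 and 0.8 if the within-subject residual is used (critical value q(10, 80)/√2 = 3.25);
- one arm different from prematch at a recovery time while the other was not, in 50–56% of trials (Tukey over 10 cells, residual error).

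**4. Multiplicity over five outcomes.** With one HRW test each, independent: 1 − 0.95⁵ = 0.226. With water and interaction both counted: 1 − 0.95¹⁰ = 0.401. Simulated with 11 or 12 per arm, within-subject correlation 0.5 or 0.7 and between-outcome correlation 0 or 0.5:

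- interaction alone, 18.1–22.8%;
- water alone, 18.0–23.5%;
- either, 33.1–41.3%.

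**5. After the change.** Using the interaction as the only HRW test gives 5% per outcome but still 22.6% over five independent outcomes. One primary outcome brings this to 5%. Bonferroni over five, 0.05 / 5 = 0.01 each, holds it at or below 5%. Changing the trigger therefore does not solve the multiplicity, and ranking the outcomes does not repair the trigger.

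**The case against.** The strongest reply is that the hypothesis test is in the plan: the interaction is fitted, and the model as a whole is said to assess acute and residual fatigue. Only the sentence on follow-up is deficient. This stands, and it limits the point to that sentence.

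A reader might go further and infer that false HRW claims are likely. The documents do not support that. Under the literal rule, a time effect leads to no HRW–placebo comparison, and a water effect adds nothing to its F test, so the rule itself creates no extra false claims. The 50–56% figure needs an inference from within-arm significance that the article nowhere proposes. The 9–33% figures need a within-subject error for a between-player comparison, which the article does not specify; with a pooled error the rate is about 1% per outcome. The time profile behind these figures is assumed.

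The two readings are also alternatives. Either between-arm follow-up is missing, or it exists but is opened by the wrong term; both harms cannot be charged at once. What remains is that the article does not say which reading applies, and neither ties follow-up to the interaction.

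On multiplicity, the article is condensed, and a full protocol or SAP may rank the outcomes or adjust for them. That part is therefore secondary and conditional. The jump test's mention of both a best attempt and an average might also suggest a choice of scores, but it can be read as averages taken within the best of three sets, so nothing here rests on it.

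**Conclusion.** The point holds as a defect in a stated rule. The post hoc trigger names time and water and omits the interaction on which the hypothesis and sample size rest. Literally followed, a real interaction produces no between-arm comparison after the match or during recovery. This needs no simulation and no assumption about documents not shown.

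The multiplicity figure is about 18–24% for at least one false HRW finding with one HRW test per outcome, and up to about 40% if the water main effect also counts. It assumes five outcomes, no HRW effect, between-outcome correlation of 0 to 0.5, and no ranking elsewhere. It comes from the unranked outcomes, not from the trigger.

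**What to change.** Replace the follow-up sentence with a rule on these lines:

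1. Water × time is the test of HRW and the only trigger for between-arm follow-up.
2. If it is significant, test four HRW–placebo differences in change from prematch (or prematch-adjusted differences): post-match and each of the three recovery times. Adjust by Holm. Take standard errors from the repeated-measures model that match the contrast.
3. Significance in one arm and not in the other will not be read as an HRW effect.
4. Name one primary outcome; the others are secondary.

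The list of times must be settled first: Statistical Analyses gives "time (prematch; postmatch; and 24, 36, and 72 hours post match", whereas Study Design has 48 hours for the middle recovery measurement. The two must be reconciled.

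The change is to analysis wording only. According to Blinding, batch codes stay undisclosed until after the statistical analysis, so it can be made blind. It has three costs:

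- Non-primary outcomes lose confirmatory status.
- Time-specific contrasts have limited power. At the first Holm step (0.05 / 4 = 0.0125) with 11 per arm and 20 df, the critical value is 2.74, and 80% power needs a difference of about 1.55 SD of the quantity compared. For a change score with SD √(2(1 − ρ)) times the single-time SD, that is 1.55 × √1.0 = 1.55 single-time SDs at ρ = 0.5 and 1.55 × √0.6 = 1.20 at ρ = 0.7.
- The first packs are taken 24 hours before the match, ahead of the prematch measurement. An effect already present then and constant afterwards would appear in the water main effect, not in the interaction. If that effect is of interest, list it as a separate secondary test.
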